### Recruitment

Patients admitted to the ICU will be examined daily during the ICU stay, and, if they meet the eligibility criteria, they or their authorized representative(s) will be contacted for consent. If consent is initially obtained from an authorized representative (e.g., in the case of a comatose, deeply sedated or delirious patient), consent will be ratified once the patient is mentally competent, defined as GCS ≥ 13, RASS between -1 and + 1, and CAM-ICU-7 ≤ 2. Patients who refuse to participate, those whose authorized representatives refuse to participate, and those who refuse to participate even though their authorized representatives have given prior consent will be excluded.

### Allocation and blinding

After initial consent, patients will be assigned to one of the two study arms using the Research Electronic Data Capture (REDCap) randomization module. A blinded study coordinator, who will not be involved in patient care, intervention, data collection or assessments, will manage this computer-generated procedure. Due to the characteristics of the intervention, neither other study staff nor patients will be blinded. Data collection and assessments will also not be blinded. However, an independent statistician will perform data analysis in a blinded fashion.

### ICU data collection and assessments

The following data will be collected and assessed from ICU admission to ICU discharge or up to a maximum of 28 days after randomization by trained study staff. Collection and assessment of outcome measures for each patient will be performed by the same investigator throughout the study. If necessary, electronic medical records will be reviewed. Since patients will be admitted to the ICU, no retention problems are expected (Table 2).

**Table 2 Tab2:** Schedule of study procedures during the ICU stay

	**Day** **0**	**Day** **1**	**Day** **2**	**Day** **…**	**Day 28/ICU discharge**
**Enrollment**					
Eligibility screening	x				
Informed consent	x				
Allocation	x				
**Intervention (RGS-ICU group only)**					
Cognitive stimulation and relaxation		x	x	x	x
Mobility level of the upper extremities^a^		x	x	x	x
Physiological parameters (SpO2, RR, HR)^b^		x	x	x	x
**ICU data collection and assessments**					
Age at ICU admission		x			
Sex at ICU admission		x			
Education at ICU admission		x			
Reason for admission (principal diagnosis)		x			
Medical comorbidities at ICU admission (CCI)		x			
Severity of illness at ICU admission (SAPS 3, APACHE)		x			
Organ failure at ICU admission (SOFA)		x			
Mental status (GCS, RASS, CAM-ICU-7)		x	x	x	x
Ventilatory support (if any)		x	x	x	x
Weaning failure (if on MV)		x	x	x	x
Pharmacological treatment (type and dose in milligrams/day)		x	x	x	x
Dyspnea, pain, worry and sadness (VAS)^c^		x	x	x	x
Experienced comfort (PEECE)					x
Cognitive screening (MoCA)					x

*ICU* Intensive Care Unit, *RGS-ICU* Rehabilitation Gaming System for Intensive Care Units, *CCI* Charlson Comorbidity Index, *SAPS 3* Simplified Acute Physiology Score 3, *APACHE II* Acute Physiology and Chronic Health Evaluation II; SOFA, Sequential Organ Failure Assessment, *SpO2* Peripheral oxygen saturation, *RR* Respiratory rate, *HR* Heart rate, *GCS* Glasgow Coma Scale, *RASS* Richmond Agitation-Sedation Scale, *CAM-ICU-7* Confusion Assessment Method for the ICU-7, *MV* Mechanical ventilation, *VAS* Visual Analogue Scale, *PEECE* Patient Evaluation of Emotional Comfort Experienced, *MoCA* Montreal Cognitive Assessment

^a^Ability to lift and hold at least one upper extremity straight against gravity

^b^Continuous variables automatically monitored as part of standard ICU care to ensure the safety of the intervention

^c^Assessed once daily in patients assigned to the control (treatment as usual, TAU) group and before and after each session in patients assigned to the experimental (RGS-ICU) group, provided the patient is mentally competent

#### Sociodemographic and clinical data

Age, sex, education, reason for admission (principal diagnosis), medical comorbidities (Charlson Comorbidity Index) [50], severity of illness (Simplified Acute Physiology Score 3 and Acute Physiology and Chronic Health Evaluation II) [51–54] and organ failure (Sequential Organ Failure Assessment, SOFA) [55] at ICU admission will be collected. Sequential data including mental status (GCS, RASS and CAM-ICU-7), mobility level (RGS-ICU group only), ventilatory support (none, non-invasive or invasive), weaning failure (if on MV) and pharmacological treatment (type and dose in milligrams/days) will be collected daily. Dyspnea, pain, worry and sadness will also be assessed once a day by visual analogue scales (VAS) with a range from 0 to 10 in patients assigned to the TAU group and before and after each intervention session in patients assigned to the RGS-ICU group, provided they are mentally competent.

#### Safety and tolerability data

The safety of the intervention will be assessed by considering the number of sessions terminated early due to unsafe events in physiological parameters, analyzing SpO2, RR and HR [19]. The safety analysis will be based on expert consensus criteria for unsafe active mobilization of patients with critical illness on MV: SpO2 < 90%, RR > 35 breaths/minute and HR > 150 beats/minute, all during ≥ 5 min [56]. Out-of-range values at the start of the session or changes > 20% from baseline in any physiological parameter will also be considered unsafe events requiring that the session not be started or terminated, respectively. Failure to start a session or early termination of a session will not preclude participation in subsequent sessions if the safety criteria are met. Safety physiological parameters will be automatically displayed on bedside monitors using advanced continuous monitoring systems as part of standard ICU care. An alarm will be triggered if an unsafe event occurs. Study staff guiding and supervising the sessions will also visually check the stability of physiological parameters to ensure the safety of the intervention and that no avoidable adverse events (e.g., unintentional removal of catheters, endotracheal tubs or tracheostomy cannulas) occur.

The tolerability of the intervention will be assessed by considering the number of completed sessions and the patients' tolerance to the interaction and workload of the cognitive and relaxation protocols. Therefore, the number of interruptions, the cause of the interruption (e.g., fatigue, extreme sleepiness, confusion), as well as the type and difficulty level of the cognitive and relaxation protocols in which the interruption occurred will be recorded.

#### Cognitive screening and experienced comfort data

On the day of discharge from the ICU, all participants will be administered the PEECE, a 12-item self-report questionnaire assessing subjective psychological well-being (Cronbach’s alpha = 0.74–0.88) [36]. The Montreal Cognitive Assessment (MoCA) test, a validated cognitive screening in survivors of critical illness, will also be administered [57, 58]. These data will only be collected if the patient is mentally competent.

#### Post-ICU assessments

The following data will be assessed three and 12 months after ICU discharge by trained study staff. Patient assessments after ICU discharge will be performed by the same investigator who followed them during their ICU stay. To promote retention, patients will be contacted by telephone to personally schedule follow-up visits. If the patient does not keep the first appointment, a second visit will be scheduled (Table 3).

**Table 3 Tab3:** Schedule of study procedures after the ICU stay

	**3 months after ICU discharge**	**12 months after ICU discharge**

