#### Data management and confidentiality

Case Report Forms (CRFs) will be kept in locked file cabinets and all data will be entered in electronic CRFs (eCRFs) in a study-specific REDCap database protected by username and password. Patients will always be identified by a code, so that clinical data concerning them will never be linked to their personal data. In addition, personal and non-personal data will be stored in decoupled REDCap databases to ensure anonymity and confidentiality of the information collected. All records will be pseudo-anonymized and a master file linking the pseudo-anonymized data to patient identifications will be maintained within each center's network. Once this procedure has been carried out, the data will be integrated and stored in a relational database located in the servers of the University of the Balearic Islands-Research Institute of Health Science. From this moment on, aggregated and non-identifiable data will be used, maintaining a variable that is the origin of the data. The data will be securely stored in local servers protected by username and password access and will only be accessible by systems with secure virtual private network connection and secure credentials. All study staff will have access to the data for research purposes, with the obligation to maintain strict confidentiality. Data will be stored for at least 5 years after the end of the trial and then destroyed if no longer needed for research. Each partner will be responsible for data management in its respective center. Harmonization workshops will be organized to ensure that data are collected, assessed, and managed in a homogeneous manner. The staff trained to administer the intervention, collect and assess patient outcomes will be four investigators, two at the Parc Taulí University Hospital and two at the Son Llàtzer University Hospital.

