## Discussion

This is a two-arm, parallel-group, superiority RCT aimed at evaluating the efficacy and safety of receiving early cognitive stimulation and relaxation as an adjunct to standard ICU care compared to receiving standard ICU care alone. This trial responds to the need to humanize intensive care [64], a new paradigm of human-centered ICU care that aims to actively involve patients in their recovery process, as intended by the RGS-ICU intervention.

This RCT builds on previous PoC and clinical pilots that demonstrated that neuropsychological e-health interventions based on VR techniques, whether immersive or not, used as an adjunct to standard ICU care, in addition to being safe for patients with critical illness [19], can help reduce anxiety during the ICU stay [20], as well as improve working memory performance after ICU discharge [13]. However, these studies were limited by methodological issues such as single-center designs, small sample sizes (n ≤ 21 subjects per group), heterogeneous diagnoses, interventions that included cognitive but not relaxation protocols, and absence of assessment of variables such as experienced comfort, subjective cognition, functionality and HRQoL.

In an attempt to overcome these limitations, the RGS-ICU trial has been designed, whose main strengths include a multicenter design, strict inclusion/exclusion criteria, an adequately powered sample size to test the primary outcome (i.e., objective cognition 12 months after ICU discharge), the use of an enhanced and optimized e-health intervention combining cognitive protocols to stimulate the brain with relaxation videos to promote stress and anxiety reduction, and the administration of a full neuropsychological battery to characterize the cognitive, mental health, functional and HRQoL profile of survivors of critical illness. This trial will also benefit from monitoring patients' physiological parameters as part of standard ICU care to ensure the safety of the intervention and that it is adapted to their mental status and mobility level in real time. In contrast, its open design is a limitation that will be compensated by blinding the data analysis by an independent statistician. Following SPIRIT guidelines for reporting study protocols [22], the sample size has been calculated for the primary outcome, so the study may be underpowered for test other outcomes. The use of self-reported measures to assess mental health may also be a limitation of the study.

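### The 12-month primary battery must be given unblinded by the investigator who followed the patient in the ICU, and a blinded analysis cannot compensate for that

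*Protocol article*

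**What the plan says.** Four statements in the Protocol article determine who measures the primary endpoint.

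- **Post-ICU assessments** (3 and 12 months): "Patient assessments after ICU discharge will be performed by the same investigator who followed them during their ICU stay".
- **ICU data collection and assessments**: "Collection and assessment of outcome measures for each patient will be performed by the same investigator throughout the study".
- **Allocation and blinding**: "Due to the characteristics of the intervention, neither other study staff nor patients will be blinded", followed by "Data collection and assessments will also not be blinded". Only the coordinator who manages randomisation and the statistician are blinded.
- **Data management and confidentiality**: "The staff trained to administer the intervention, collect and assess patient outcomes will be four investigators", with "two at the Parc Taulí University Hospital and two at the Son Llàtzer University Hospital".

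Under Outcomes, the primary endpoint is a global cognition z-score at 12 months. It is built from digit span forward and backward, RAVLT, TMT, Stroop, FAS fluency, Digit Symbol-Coding and SDMT.

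The Discussion names the lack of blinding as a weakness and offers one remedy: "its open design is a limitation that will be compensated by blinding the data analysis by an independent statistician".

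**The concern.** In every test of the primary index, an examiner presents material, keeps time, encourages or prompts, and decides what counts as a correct response. An examiner who knows the arm, and works in a team that hopes the intervention helps, can influence each of these steps without intending to. The same-investigator rule makes that knowledge certain for every patient.

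The reason given for not blinding is the nature of the intervention. That explains why patients and session staff cannot be blinded. It does not explain why the tester must be unblinded at 12 months, long after the sessions have ended.

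Blinding the statistician protects against selective analysis. It does nothing about a shift introduced when the test was given, timed or scored. Such a shift would be part of the estimated group difference, and nothing in the planned analysis could separate it from a treatment effect. A positive result would be open to that objection.

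**Working it through.** **1. The statements read together.** Post-ICU assessments and ICU data collection and assessments give each patient one assessor for the whole study. Allocation and blinding leaves that assessor unblinded. It is therefore explicit that the 12-month assessor knows the allocation. Data management and confidentiality describes one pool of four people trained for both delivery and assessment, so overlap between the two tasks is likely for a given patient. That last step is inference.

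**2. The plan's own sample size.** Inputs from Sample size and power calculation: eta squared 0.14, Cohen's d 0.8, two-sided alpha 0.05, power 0.80, 26 per group.

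- Conversion: d = 2 × √(0.14 / 0.86) = 0.807, stated as 0.8.
- Two-sample t-test, noncentral t distribution, d = 0.8: 25 per arm gives power 0.791 and 26 per arm gives 0.807. The stated 26 per group is reproduced.

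**3. The effect of a measurement shift.** Let the true difference be zero and let assessment move the RGS-ICU mean upwards by b standard deviations. With n = 26 per arm, df = 2 × 26 − 2 = 50 and the noncentrality parameter is b × √(26/2) = b × √13 = 3.606 b. The chance of p < 0.05 is the probability that this noncentral t falls outside the usual two-sided limits.

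| Assumed shift b (SD) | Noncentrality | Two-sided false-positive rate | Of which in favour of RGS-ICU |
|---|---|---|---|
| 0 | 0 | 5.0% | 2.5% |
| 0.1 | 0.361 | 6.4% | 5.4% |
| 0.2 | 0.721 | 10.9% | 10.5% |
| 0.3 | 1.082 | 18.6% | 18.4% |

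The article gives no size for such a shift, so the values of b are assumptions. For scale, 0.2 SD is a quarter of the anticipated effect (0.2 / 0.8 = 0.25). As b grows, almost all the false positives come to favour RGS-ICU.

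**4. The proposed remedy.** Blinded analysis enters none of these quantities: b is fixed once the tests have been scored. Masking the assessor acts on b itself.

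**The case against.** The strongest reply has five parts.

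- **Who ran the sessions.** A reader might infer that the follow-up assessor is certainly the person who delivered that patient's sessions. The documents do not say so. The rule speaks of the investigator who followed the patient, and Experimental condition: RGS-ICU group lists clinical staff among those guiding sessions. This stands, and the point does not depend on it, because the assessor is unblinded either way.
- **Rapport in both arms.** A reader might also infer that familiarity with the assessor exists only in the RGS-ICU arm. That is contradicted. Controls have daily mental status and VAS ratings, then PEECE and MoCA at ICU discharge, under the same one-investigator rule. The arms differ in amount of contact (sessions, and VAS before and after each) and in expectation of benefit. This stands.
- **Feasibility of masking.** It is tempting to say that the existing staff make the problem fully avoidable. The documents do not show this. Each hospital has two investigators, sessions run daily for up to 28 days, cross-cover is likely, patients know their arm, and all study staff have access to the data. Masking would be partial. It would still be better than a rule that excludes it.
- **Limits on examiner influence.** The tests are validated, scored against population norms, and supported by harmonization workshops. This lowers the risk without removing it, and is a reason to treat the shifts above as illustrations.
- **Continuity and disclosure.** A familiar assessor might help attendance when 35% loss after ICU discharge is expected, and a single examiner avoids variation between visits. The article ties retention to telephone contact and rescheduling, and one masked assessor can do both visits. The open design is disclosed, but the remedy offered for it does not work.

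**Conclusion.** The concern holds in this form: the protocol requires unblinded assessment of its primary endpoint by the investigator who followed the patient in the ICU, and its statement that blinded analysis compensates is incorrect. Knowledge of allocation is explicit. Delivery of sessions by the same person is likely but not stated, and scoring by that person is implied by the assessment role without being spelled out.

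The figures of 6.4%, 10.9% and 18.6% against 5% rest on three assumptions: no true effect, 26 evaluable patients per arm, and shifts of 0.1, 0.2 and 0.3 SD towards RGS-ICU. They show how sensitive the test is. They are not an estimate of the bias, and the documents do not establish that bias will occur. The matter should be settled before follow-up data are collected, because it cannot be repaired afterwards.

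**What to change.** 1. For post-ICU outcomes, replace the same-investigator rule in ICU data collection and assessments and in Post-ICU assessments. Both follow-up batteries are administered and scored by the hospital's other trained investigator, who as far as the rota allows has not run or observed that patient's sessions. The same assessor does the 3- and 12-month visits.
2. Amend Allocation and blinding to say that follow-up assessors are masked to allocation where possible.
3. Restrict that assessor's access to allocation and session data, since Data management and confidentiality now opens the data to all study staff. Ask patients not to reveal their arm. Record the assessor's guess of allocation and any unmasking.
4. Let the familiar investigator keep making the retention calls.
5. Delete the Discussion's statement that blinded analysis compensates for the open design, and report unblinded or imperfectly masked assessment as a remaining limitation.

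Cost: a protocol amendment, a rota change among the four existing investigators and a change to data permissions. No added staff are assumed, and the figures of 26 evaluable per group and 80 recruited do not change. The downsides are less continuity with the patient and imperfect masking in a two-person site team.

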**Post-ICU assessments**		
Cognitive reserve (CRQ)^a^	x	
Estimated IQ (NART)^a^	x	
Cognitive screening (MoCA)	x	x
Attention (WAIS-IV Forward Digit Span subtest)	x	x
Working memory (WAIS-IV Backward Digit Span subtest)	x	x
Learning/memory (RAVLT)	x	x
Executive function (TMT, SCWT, FAS)	x	x
Processing speed (WAIS-IV Digit Symbol-Coding subtest, SDMT)	x	x
Subjective cognition (PDQ-5)	x	x
Anxiety (GAD-7)	x	x
Depression (PHQ-9)	x	x
PTSD (TOP-8)	x	x
Functionality (WHODAS 2.0)	x	x
HRQoL (SF-12)	x	x

*ICU* Intensive Care Unit, *MoCA* Montreal Cognitive Assessment, *CRQ* Cognitive Reserve Questionnaire, *NART* National Adult Reading Test, *WAIS-IV* Wechsler Adult Intelligence Scale-IV, *RAVLT* Rey Auditory Verbal Learning Test, *TMT* Trail Making Test, *SCWT* Stroop Color and Word Test, *FAS* Verbal phonemic fluency test, *SDMT* Symbol Digit Modalities Test, *PDQ-5* Perceived Deficits Questionnaire-5, *GAD-7* Generalized Anxiety Disorder-7, *PHQ-9* Patient Health Questionnaire-9, *PTSD* Posttraumatic stress disorder, *TOP-8* Treatment-Outcome Post-Traumatic Stress Disorder Scale, *WHODAS 2.0* 12-item World Health Organization Disability Assessment Schedule 2.0, *HRQoL* Health-related quality of life, *SF-12* 12-item Short-Form Health Survey

^a^If not evaluated at 3 months due to non-attendance at the follow-up visit, it will be evaluated at 12 months

#### Cognition

Cognitive reserve will be assessed with the 8-item self-reported Cognitive Reserve Questionnaire (CRQ) (range 0–25) (Cronbach’s alpha = 0.80–0.96) [59, 60] and intelligence quotient (IQ) with the National Adult Reading Test, which provides a reliable estimate of premorbid IQ (*r* = 0.69–0.81) [61, 62]. CRQ and estimated premorbid IQ data will only be collected once at three or 12 months of follow-up.

Objective cognition will be assessed with the MoCA screening test [57, 58] and a comprehensive battery of validated neuropsychological tests including measures of attention (WAIS-IV Forward Digit Span subtest), working memory (WAIS-IV Backward Digit Span subtest), learning/memory (RAVLT), executive function (TMT, SCWT and FAS) and processing speed (WAIS-IV Digit Symbol-Coding subtest and SDMT). Raw data from neuropsychological tests will be standardized using population-based norms [30–35] and combined into a composite index of global cognition (z-score) established on the basis of previous studies [6–8, 13, 14].

Subjective cognition will be assessed with the 5-item self-reported PDQ-5 questionnaire (Cronbach’s alpha = 0.81–0.96) [37, 38].

#### Mental health

Anxiety will be assessed with the 7-item self-reported GAD-7 questionnaire (Cronbach’s alpha = 0.92–0.94) [39, 40], depression with the 9-item self-reported PHQ-9 questionnaire (Cronbach’s alpha = 0.86–0.89) [41, 42] and PTSD with the 8-item hetero-administered TOP-8 scale (Cronbach’s alpha = 0.79) [43, 44].

#### Functionality and HRQoL

Functionality will be assessed with the 12-item self-reported WHODAS 2.0 schedule (Cronbach’s alpha = 0.94–0.98) [45] and HRQoL with the 12-item self-reported SF-12 survey (Cronbach’s alpha = 0.69–0.70) [46, 47].

#### Additional variables

For each cognitive stimulation and relaxation session with the RGS-ICU platform, the start and end time, the protocols performed, the duration of each protocol, the difficulty levels performed (only cognitive protocols), the number of hits and failures per difficulty level (only cognitive protocols), and the number and reasons for interruption and/or early termination of the sessions (if applicable) will be recorded.

The following data will also be collected: days of delirium and invasive MV, days of ICU and hospital stay, discharge destination (home, home hospitalization or social-health center), days to return to work after ICU discharge (working age patients only), number of hospital and ICU readmissions, and need for psychopharmacological treatment, psychotherapy, cognitive rehabilitation and physical rehabilitation after ICU discharge.

These data will be collected at ICU discharge or during post-ICU follow-up visits, as appropriate. If necessary, electronic medical records will be reviewed (Table 4).

**Table 4 Tab4:** Additional variables collected during and after the ICU stay

	**Day** **1**	**Day** **2**	**Day** **…**	**Day 28/ICU discharge**	**3 months after ICU discharge**	**12 months after ICU discharge**
**Intervention characteristics (for each session)**^a^						
Star and end time	x	x	x	x		
Protocols performed	x	x	x	x		
Duration of each protocol	x	x	x	x		
Difficulty levels performed (only cognitive protocols)	x	x	x	x		
Number of hits and failures per difficulty level (only cognitive protocols)	x	x	x	x		
Number and reason for interruption or early termination (if applicable)	x	x	x	x		
